#### 4. Statement of Compliance

The clinical trial will be conducted in compliance with the following guidelines and documentation:

- [ICH Guidelines for Good Clinical Practice \(GCP\)](#)
- [National Statement on Ethical Conduct in Human Research](#) (National Statement)
- As approved by the Human Research Ethics Committee (HREC), the clinical trial protocol is responsible for monitoring the trial's conduct.
- The responsibilities set out by the UNSW Sponsors Delegate.

The onsite or remote monitoring standard operating procedures as put in place by the clinical trial sponsor.

The coordinating principal investigator accepts responsibility for the accuracy of the information provided in this application and ensures that the qualifications and/or experience of all members of the iDBT-Pain research team involved with the project are appropriate to their role. The coordinating PI will ensure that all tasks will only be delegated to appropriately trained, skilled, and qualified staff. The PI will remain responsible for the overall study conduct and reported data, ensuring study oversight. All associates, colleagues, and employees assisting in the conduct of the study will be informed about their obligations and will not perform any study tasks before appropriate delegation and completion of appropriate training. All research staff will receive the appropriate information and training throughout the study and a 2-way communication channel will exist between staff and the PI. Any delegation of staff or changes in staff will be recorded promptly in the Clinical Trial Delegation and Responsibilities Log (see 22. Clinical Trial Delegation and Responsibilities Log). iDBT-Pain researchers will maintain valid ICH Good Clinical Practice certification for the duration of the trial. [name], [name], [name], [name], and [name] have completed the "Introduction to Good Clinical Practice" Course. (Certificates are filed in the eTMF [electronic Trial Master File]).

#### 5. Trial Design

- [Describe the selected trial design \(e.g., double-blind, placebo-controlled, parallel design\) and justify how it will meet the clinical trial aims.](#)

This trial is a pilot randomised controlled trial with participants with chronic pain randomised to one of two arms: 'treatment' and 'treatment-as-usual'. Efficacy of iDBT-Pain will be determined by comparing treatment to treatment-as-usual for the primary and secondary outcomes. Treatment-as-usual is defined as any of the treatment options offered by the healthcare professionals' that participants would normally access in the community.

- [Describe the measures to be implemented to minimise and avoid bias \(e.g. randomisation, blinding\)](#)

Forty-eight participants will be recruited to the study (see 6. Sample Size). Following informed consent, and before baseline assessment participants will be randomly allocated to groups (treatment or treatment-as-usual) in blocks of 6. A randomisation schedule will be created in Excel by the statistician who is not involved in the recruitment, treatment, or data collection to minimise risk of bias.

Allocation of participants to randomisation schedule: Participants will have been assigned a participant ID in Qualtrics during the study screening process (see Section 7.4). This ID will be provided to a member of the research team to be added in the next available cell in the randomisation schedule Excel sheet. The member of the research team that adds the participant ID to randomisation schedule Excel sheet will not have access to any information about the participant except the participant ID and will not be involved in the recruitment, treatment, or data collection. Once the participant has been added to the Excel sheet, the team member will advise the skills trainer of the participants group allocation and the group allocation will be updated by the skills trainer in Qualtrics. The skills trainer will communicate the group allocation to each participant by phone or email.

- Provide a schematic diagram of trial design, procedures, and stages.

[figure not shown]

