## 6. Sample Size

The plan is to enrol 100 subjects to complete the trial. The nominated sample is based on a sampled size calculation using SAS 9.4 conducted by biostatistician [name] (UNSW Mark Wainwright Analytical Centre). To calculate sample size for the current trial the effect size from our pilot data from the secondary outcome (pain intensity, effect size = .82) (Norman-Nott et al. 2021) has been used as it had a lower effect size than the primary outcome (i.e., emotional dysregulation, effect size = .88). To detect a mean difference of effect size 0.7 between treatment groups in the secondary outcome (i.e., pain intensity), a total of 100 people (50 in each group) will be required. This assumes 80% power, alpha of 0.05 and a within-subjects correlation of 0.2. This aligns with the recommendation for pilot trials in clinical/translational research that states that the number of participants required for a pilot trial is approximately 20-50 per arm (Moore et al., 2011). To account for an expected 15-20% attrition, the total sample size is 100.

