Treatment-as-usual: Participants in the treatment-as-usual condition may receive treatment options that can be any of those offered by the healthcare professionals they would normally choose to consult with in the community. In other words, the participants in the treatment-as-usual condition will be advised they will not receive treatment determined by the study or funded by it. It will be explained to the participants that the role of being in this group is very important to the study because the outcomes gained by this group set the bar to know whether the intervention (iDBT-Pain) is any better or not. It will further be explained to these participants that they will have access, at the study conclusion (e.g., following the 3-month follow-up assessment), to the iDBT-Pain web app accessible via their own smart device.

*Data Collection Procedure:* Assessment times for both the treatment and treatment-as-usual conditions will be at baseline, post-intervention (9-weeks post baseline assessment) and at 3 months following the post-intervention assessment. Baseline assessment will begin once 24 participants are in a group and randomised. Assessments will encompass self-report questionnaires (see section 10.1), and eligible participants will be invited to undertake MRI scanning. Questionnaires will be completed online via Qualtrics survey platform and will take a maximum of 90 minutes to complete. MRI scanning will be in-person at NeuRA, Sydney (see section 10.1). Participants will be advised that if they cannot or choose not to participate in the MRI they may still participate in all other aspects of the study. Additionally, post-intervention, qualitative data will be collected from participants in the treatment condition via a semi structured interview with a member of the research team via Zoom or phone call.

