*Treatment Condition:* Participants in the treatment condition will receive the iDBT-Pain intervention. The iDBT-Pain intervention involves one 60-90 minute introductory session, six 60-90 minute iDBT-Pain sessions delivered by a DBT skills trainer via Zoom in groups of 8 to 12 participants, and one concluding session delivered weekly (every 7 days) over eight weeks. As part of the iDBT-Pain intervention, for the duration of the eight weeks, and for one week after the concluding Zoom session, participants will have continued access to a web app (iDBT-Pain web app) which participants will access on their own smart device (e.g., iPhone or computer) with their own secure password and username. The iDBT-Pain app includes videos and tasks to encourage skills practice between the Zoom sessions and to maintain the skills in the week

following the concluding session. Participants will be provided with a set of clear instructions to set up the app and to access the sessions (Attachment 9).

*Fidelity and Consistency Across Treatment Groups:* Participants in the treatment condition will be in one of two skills training groups consisting of 12 participants for their iDBT-Pain sessions. The structured protocol (see section 10.1) for the iDBT-Pain sessions will ensure treatment fidelity and consistency across the two groups to mitigate effects of confounding factors that may arise due to different groupings.

*Treatment-as-usual condition:* In contrast to the treatment condition, the treatment-as-usual condition will receive no intervention as part of the trial. Participants in the treatment-as-usual condition may receive treatment options as offered by the healthcare professionals they would normally consult with in the community (see Section 10).

Upon conclusion of the study (e.g, following 3-month assessment) all participants will retain (if in the treatment group) or receive (if in the treatment-as-usual group) access to the iDBT-Pain app for personal use on their own smart device.

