## 12. Statistics

- Describe the statistical plan for analysing the trial data.

*Data Analysis Plan:* For all primary and secondary outcomes that are normally-distributed and measured over time, a linear mixed model with random effect of individuals will be specified. Fixed effects of time, treatment group and the interaction will be included. Treatment differences at 9 weeks and at 21 weeks and change from baseline to 9 and 21 weeks within each group will be estimated. If the distributional assumption of normality is not tenable, an appropriate transformation of the outcome will be conducted. Alternatively, a generalized linear mixed model with appropriate distribution and link will be used.

The data will be analysed on an intention-to-treat basis. Unadjusted and adjusted analyses will be conducted. Adjusted analyses will include age at baseline and gender. P-values <0.05 will be considered significant.

*MRI Data Analysis Plan:* Quantification of neurotransmitter ratios of the acquired spectra will be analysed using the Java-based magnetic resonance user's interface (jMRUI 6.0, European Union project). To examine differences between periods, 2 Time (Baseline, Post) repeated-measures (RM)-ANOVA on neurotransmitter ratios will be used ( $p < 0.05$ ). Blood oxygen level

dependent (BOLD) imaging, Structural Imaging and Quantitative Arterial Spin Labelling (QASL) will be analysed using Statistical Parametric Mapping (SPM12). Significant differences between periods, 2 Time (Baseline, Post) will be determined using a random effects analysis, false discovery rate,  $p < 0.05$ .

We also aim to determine necessary amendments to the iDBT-Pain skills training based on the qualitative feedback from the interview with the treatment group. This data will be analysed by the investigators and summarised on a form for future development and iterations of the iDBT-Pain intervention.

- Indicate the timing of any planned interim analyses.

There is no planned interim analyses.

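### Sections 5 and 8 recruit 48 participants and Section 10.1 provides skills groups for 24 treated, but Section 6 requires 100 (50 per arm) for 80% power

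*Protocol*

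**What the plan says.** Section 5 (Trial Design) states: "Forty-eight participants will be recruited to the study (see 6. Sample Size". The Randomisation Procedure in Section 8 repeats the sentence. Both then set blocks of 6.

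Section 6 (Sample Size) states: "The plan is to enrol 100 subjects to complete the trial". It bases this on a standardised effect for a secondary outcome: "To detect a mean difference of effect size 0.7 between treatment groups in the secondary outcome (i.e., pain intensity), a total of 100 people". It adds: "This assumes 80% power, alpha of 0.05 and a within-subjects correlation of 0.2". The allocation is explicit: "a total of 100 people (50 in each group) will be required". Expected attrition is 15 to 20%.

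Section 10.1 (Trial Intervention), on fidelity across treatment groups, states: "Participants in the treatment condition will be in one of two skills training groups consisting of 12 participants for their iDBT-Pain sessions". The sentence after it again speaks of two groups. Section 8 caps a skills group at 12.

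Section 8 (Data Collection Procedure) states: "Baseline assessment will begin once 24 participants are in a group and randomised". Section 10.1 uses the same count of 24 to start the intervention.

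The amendment history records an August 2023 change of sample size, made to improve power. The protocol is version 6, dated 23/08/2023.

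**The concern.** The sections that govern recruitment and randomisation give a number that contradicts the section they cite. The skills-group sentence contradicts Section 6 separately, and it carries no cross-reference that would send the reader to the right figure. The conflict lies between passages of the current text. The amendment history only suggests how it arose: the new target reached Section 6 but not the operational sections.

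The enrolment target has to be unambiguous because the protocol claims a stated power, says efficacy will be determined by comparing the arms, and tests formally ("P-values <0.05 will be considered significant"). If 48 were followed, the trial would fall well short of the power that Section 6 claims. If 100 is followed, the group structure described for the treated arm holds fewer than half of the treated participants.

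**Working it through.** **Inputs.** From Section 6: effect 0.7 (SD taken as 1), 80% power, alpha 0.05, within-subject correlation r = 0.2, equal arms, attrition 15 to 20%. From Sections 5 and 8: total 48. Two-sided testing is assumed because sidedness is not stated. The test behind 100 is not named either, so several readings are shown.

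**Can 100 be reproduced?** The number per arm is n = 2v(1.960 + 0.842)²/0.7², where v is the variance of the quantity compared and (1.960 + 0.842)² = 7.849.

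- Raw 9-week score, v = 1: n = 32.04, so 33 per arm and 66 in total; 66/0.8 gives 83. This does not reproduce 100.
- Baseline-adjusted 9-week score, v = 1 − 0.2² = 0.96: n = 30.8, so 31 per arm and 62 in total; 62/0.8 gives 78. This does not reproduce 100.
- Change from baseline to 9 weeks, v = 2(1 − 0.2) = 1.6: n = 51.3, or 102.5 in total before rounding up. At 50 per arm, power is 79% (normal approximation) or 78% (t). This is close to the stated 80%, with no attrition allowance.
- Mean of both follow-ups minus baseline, v = 0.6 + 1 − 0.4 = 1.2: n = 38.4, so 39 per arm and 78 in total; 78/0.8 gives 98. This is close to 100 with attrition included.

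So 100 is recoverable, to within rounding, only under the two change-type readings.

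**Power at 48 and at 100 on the same basis.** Noncentral t with 2n − 2 degrees of freedom and noncentrality 0.7√(n/2)/√v. A 20% loss takes 24 to 19 per arm and 50 to 40 per arm.

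| Total | n per arm analysed | Raw 9-week: noncentrality | Power | Change, r = 0.2: noncentrality | Power |
|---|---|---|---|---|---|
| 48 | 24 | 2.42 | 66% | 1.92 | 47% |
| 48, 20% loss | 19 | 2.16 | 56% | 1.71 | 38% |
| 100 | 50 | 3.50 | 93% | 2.77 | 78% |
| 100, 20% loss | 40 | 3.13 | 87% | 2.47 | 69% |

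Other readings at 24 per arm, with 19 per arm after the comma: baseline-adjusted 68%, 57%; mean of both follow-ups minus baseline 58%, 48%. On the raw 9-week comparison, the smallest effect that 24 per arm detects with 80% power is 0.83.

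Only averaging scores across assessments, without subtracting baseline, keeps 48 near or above 80%. The mean of the two follow-ups gives 87% at 24 per arm and 77% at 19. That reading would need only 40 participants in total, so it cannot be the source of 100, and it is not the 9-week primary endpoint.

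**Where 48 may come from.** With the pilot effect of 0.82 quoted in Section 6 and v = 1, n = 2 × 7.849/0.82² = 23.3, so 24 per arm and 48 in total. This fits a superseded target left in place, but the document does not say so.

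**Skills groups.** Two groups of 12 hold 24 treated participants, half of 48. Fifty treated participants at 12 per group need 50/12 = 4.17, so at least five groups.

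**The case against.** The strongest defence is that the discrepancy resolves itself. Both sentences giving 48 point to Section 6, Section 6 is clear about 100, and the amendment history shows that the size was deliberately changed. A careful reader will see that 48 is the leftover. This has force: the fault is incomplete updating after an amendment, and it cannot be assumed that the team will stop at 48. But no rule of precedence is stated, and the skills-group sentence has no pointer to Section 6.

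Several stronger readings are tempting and are not supported:

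- A reader might infer that blocks of 6 are built for 48, since 48 is eight blocks and 100 is not a whole number of them. Stopping partway through a last block is ordinary, and blocks of 6 do not tie the design to either number.
- A reader might infer that the schedule would run out at 48. No schedule length is given.
- A reader might infer that four participants are stranded, since four cohorts of 24 make 96. The trigger can be read as a minimum and does not say that cohorts are exactly 24 or that the count restarts. The wording is unclear, but that consequence does not follow.
- A reader might set 48 after dropout against 100 before dropout. That exaggerates the contrast: under the change reading, 100 also falls below 80% after 20% loss, at 69%.

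Calling the trial a pilot does not remove the point, since the protocol itself claims 80% power and plans formal tests.

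**Conclusion.** The point holds as a contradiction in the current text: 48 in Sections 5 and 8, and two groups of 12 in Section 10.1, against 100 in Section 6. The figure on which the trial's power rests is therefore wrong as written in the sections used to run it.

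If 48 were followed, power for the stated effect would be 47 to 66% without loss and 38 to 56% after 20% loss. With 100 it is 78 to 93% and 69 to 87%. In each range the lower figure is change from baseline and the higher is the raw 9-week difference. The ranges assume two-sided 5% testing, equal arms and r = 0.2 for the change reading. They concern pain intensity, not the primary outcome of emotion dysregulation. They describe what following the operational text would cost, not a prediction that it will be followed.

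This should be corrected before further recruitment relies on the document: the number is central and the correction is simple.

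**What to change.** - In Section 5 and in the Randomisation Procedure of Section 8, replace 48 with 100.
- In Section 10.1, replace the two groups of 12, and the later mention of two groups, with the number of groups that 50 treated participants need (at least five at the stated maximum of 12), so that the fidelity statement covers all of them.
- Confirm that the randomisation schedule covers 100. If anyone has already been randomised, extend the schedule and do not regenerate it.
- In Sections 8 and 10.1, say whether the 24-participant trigger is a minimum or applies to each cohort.

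The cost is protocol wording and, if needed, a longer schedule. No participants are added beyond the 100 that Section 6 already plans.

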## 6. Sample Size

The plan is to enrol 100 subjects to complete the trial. The nominated sample is based on a sampled size calculation using SAS 9.4 conducted by biostatistician [name] (UNSW Mark Wainwright Analytical Centre). To calculate sample size for the current trial the effect size from our pilot data from the secondary outcome (pain intensity, effect size = .82) (Norman-Nott et al. 2021) has been used as it had a lower effect size than the primary outcome (i.e., emotional dysregulation, effect size = .88). To detect a mean difference of effect size 0.7 between treatment groups in the secondary outcome (i.e., pain intensity), a total of 100 people (50 in each group) will be required. This assumes 80% power, alpha of 0.05 and a within-subjects correlation of 0.2. This aligns with the recommendation for pilot trials in clinical/translational research that states that the number of participants required for a pilot trial is approximately 20-50 per arm (Moore et al., 2011). To account for an expected 15-20% attrition, the total sample size is 100.

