## 2. Trial Objectives and Purpose

- Describe the aim(s) of the clinical trial and specify the research questions that the trial will address.

In a recent pilot study (ethics approval: HC2001990) using a single-case experimental design ( $N=3$ ) evidence was promising for the feasibility and acceptability of an online skills training for people in chronic pain (internet-delivered dialectical behavioural therapy skills training; iDBT-Pain) (Norman-Nott et al., 2021).

The purpose of the current pilot trial is to further investigate the effectiveness of iDBT-Pain for individuals with chronic pain to determine the effects on the emotional, sensory, and neurological components associated with chronic pain. The objectives of this trial are to:

1. Reduce emotion dysregulation
2. Reduce pain intensity
3. Improve psychological factors associated with chronic pain (e.g., symptoms of anxiety and depression, harm avoidance traits, sleep quality, life satisfaction, and coping behaviours)
4. Conduct exploratory investigation of changes in brain function (e.g., neurochemical levels in the medial prefrontal cortex)

We additionally aim to attain qualitative data to optimise the design of the intervention to provide crucial information for funding to facilitate future development and testing in a full-scale randomised controlled trial.

- Specify the primary endpoints and the secondary endpoints to be measured during the trial.

Participants will be randomly assigned to either a 'treatment' or 'treatment-as-usual' condition. It is hypothesised that participants in the 'treatment' condition will demonstrate a significant improvement in the primary outcome (emotion dysregulation) and secondary outcomes (pain intensity, symptoms of anxiety and depression, harm avoidance, sleep quality, life satisfaction, coping behaviours and social cognitive skills) when measured at post-assessment (primary endpoint) following the 9-week intervention, and this will remain when measured at 3-month follow-up (secondary endpoint).

A further secondary outcome is change in cortical function (e.g., changes in neurotransmitters' levels) which will be observed using magnetic resonance imaging at baseline and post assessment. A semi-structured interview will be used to gather information about participants experience of the skills training during the post-assessment.

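### Section 6 names a pilot effect of .82 as the basis for N = 100 but calculates from 0.7, and gives the same 100 both as the number required and as the number allowing for attrition

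*Protocol*

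**What the plan says.** Protocol Section 6 (Sample Size) takes its effect sizes from the group's earlier pilot. It identifies "the secondary outcome (pain intensity, effect size = .82" as the basis and says this value "has been used as it had a lower effect size than the primary outcome", for which it gives "emotional dysregulation, effect size = .88".

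The following sentence starts from a different value: "To detect a mean difference of effect size 0.7 between treatment groups in the secondary outcome". From it the protocol concludes that "a total of 100 people (50 in each group) will be required" and adds: "This assumes 80% power, alpha of 0.05 and a within-subjects correlation of 0.2". The section closes by saying that the total is 100 in order to allow for 15-20% attrition.

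Two other places bear on this. Section 2 describes the pilot as a study of three people "using a single-case experimental design". The August 2023 entry in the amendment history says that the earlier calculation rested on that very small study, that such designs can overestimate effects, and that the size was recalculated on a more conservative effect. It prints that effect as -.07 and names emotion dysregulation as the outcome.

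**The concern.** Consecutive sentences give two design effects for one outcome. The first presents .82 as the value used. The second calculates from 0.7 and neither sources it nor calls it a reduced .82. Both cannot be the effect behind N = 100, so a reader who takes the first sentence at face value will believe that the trial is sized on its pilot data.

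Checking the arithmetic brings out a second problem in the same paragraph. The figure of 100 appears first as the number required at 0.7 and then as the number that already absorbs attrition. If 100 are needed for analysis, then 100 enrolled with 15-20% lost will not supply them. At stake is whether 80% describes the trial at enrolment, at analysis, or neither.

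**Working it through.** **Inputs, all from Section 6:** effects .82 and 0.7; 50 per arm; power 80%; alpha 0.05; within-subject correlation r = 0.2; attrition 15-20%.

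**Assumptions, because the protocol does not state them:** two-sided alpha, and an effect d expressed in units of the raw between-person SD.

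**Formula.** n per arm = 2 x f x (1.96 + 0.84)^2 / d^2, where f is the variance of the analysed contrast relative to a single score. For the week-9 score alone, f = 1. For a baseline-adjusted week-9 score, f = 1 - r^2 = 0.96. For change from baseline, f = 2(1 - r) = 1.6. The t-test version uses d / sqrt(f) as the effect and adds about one person per arm. The power figures below are from the t-test.

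**Step 1: reproduce 50 per arm at 0.7.**
- Week-9 score: 2 x 1 x 7.85 / 0.49 = 32.0, so 33 per arm (34 by t-test), 66-68 in total. Power at 50 per arm is 93%.
- Change score: 2 x 1.6 x 7.85 / 0.49 = 51.3, so 52 per arm (53 by t-test), 104-106 in total. Power at 50 per arm is 78%.
- Baseline adjustment barely changes the week-9 result (94% at 50 per arm). Averaging visits lowers f to 0.6 or 0.467 and moves further from 50.

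Of the two-sided models tried, only the change score comes near 50 per arm before attrition, and it falls slightly short of 80%.

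**Step 2: the same with .82.**
- Week-9 score: 24 per arm (25 by t-test), 48-50 in total. Power at 50 per arm is 98%.
- Change score: 38 per arm (39 by t-test), 76-78 in total. Power at 50 per arm is 89%.

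At a fixed N of 100, .82 gives more power than 0.7 under either model.

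**Step 3: apply the attrition.** 100 x 0.85 = 85 and 100 x 0.80 = 80 completers, that is 42.5 and 40 per arm.

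| Model | Effect | Needed per arm (t-test) | Power at 50 per arm | Power at 42.5 per arm | Power at 40 per arm |
|---|---|---|---|---|---|
| Change score | 0.7 | 53 | 78% | 71% | 69% |
| Change score | .82 | 39 | 89% | 84% | 82% |
| Week-9 score | 0.7 | 34 | 93% | 89% | 87% |
| Week-9 score | .82 | 25 | 98% | 96% | 95% |

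**Step 4: can 100 be the figure after attrition?** On the week-9 model, 66-68 inflates to 78-85, below 100. On the change-score model, 106 inflates to 106 / 0.85 = 125 up to 106 / 0.80 = 133, above 100. A one-sided change-score test would need 82-84, or 97-105 after inflation, which brackets 100, but the protocol does not state a one-sided test. With .82, the two-sided change-score total of 76-78 inflates to 90-98.

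**Step 5: where the .82 sentence may come from.** The week-9 normal formula at .82 gives 48 in total. Sections 5 and 8 still say that forty-eight participants will be recruited. This suggests, without proving it, that the .82 sentence survives from before the August 2023 recalculation.

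**The case against.** The strongest reply is that the power claim is not ambiguous. The 100, the 50 per group, the 80%, the alpha and the correlation all follow from 0.7, and the amendment history explains why the design value was set below the pilot's. This stands. A reader might infer that nobody can tell which effect the trial is powered for, or that the 80% hangs on choosing between .82 and 0.7. The text does not support that, and choosing .82 would only improve power at N = 100.

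It can also be said that the 69-71% does not come from the two effect sizes at all. That too is right. It comes from using 100 twice, and would remain if the .82 sentence were deleted. It also needs an assumed change-score model. Section 12 plans treatment differences at 9 and 21 weeks, and on a week-9 comparison power stays at 87-89% after attrition. That reading shows no shortfall, but it does not reproduce 50 per arm either.

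A further inference to avoid is that a three-person single-case pilot cannot yield a usable between-person effect size. The protocol does not say how .82 and .88 were standardised, and its source is not at hand, so this cannot be judged. Nor does the protocol claim that .82 being below .88 proves that sizing on pain covers the primary outcome. It says only that the lower value was chosen.

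What remains is the contradiction in current text and the double use of 100.

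**Conclusion.** The point holds in limited form. Section 6 states one effect as the basis of the sample size and calculates from another. The likely explanation is a sentence left behind when the calculation was revised. The 80% power belongs to 0.7.

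The consequence that can be sized is attrition. Assuming two-sided alpha 0.05 and a raw-SD effect of 0.7, expected power with 80-85 completers is about 69-71% if the calculation was for a change score with r = 0.2, and 87-89% if it was for a week-9 comparison. The protocol does not say which, and neither two-sided model makes 100 both the number required and the number after attrition.

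The outcome behind 0.7 also needs settling, since Section 6 attaches it to pain and the amendment history names emotion dysregulation. That difference from a change log is not counted as an error here. It is a reason for Section 6 to be explicit. Nothing in this shows that 100 participants are too few.

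**What to change.** In Section 6:

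1. Delete or reword the sentence presenting .82 as the value used. State 0.7 as the single design value, and say that it was lowered from the pilot estimates and why.
2. Name the outcome to which 0.7 applies, reconciling pain intensity with the emotion dysregulation named in the August 2023 entry, and check the -.07 printed there.
3. State the sidedness of alpha, the variance model, and how the correlation of 0.2 enters.
4. Keep N = 100. Give the required n before and after 15-20% attrition as separate figures, and the power expected with 80-85 completers.

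The cost is a re-run of the existing calculation and a wording amendment, with no extra participants. The downside is that the restated power may be less favourable than 80%, and the pilot estimates will no longer appear as the direct source of the design effect.

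### Section 6 uses 100 both as the number required for 80% power and as the total after 15-20% attrition, and does not name the contrast, so the stated power cannot be confirmed

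*Protocol*

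**What the plan says.** The relevant text is one paragraph, Protocol Section 6 (Sample Size). It opens with "The plan is to enrol 100 subjects to complete the trial". After the effect size of 0.7 for pain intensity, it states that "a total of 100 people (50 in each group) will be required". The assumptions follow: "This assumes 80% power, alpha of 0.05 and a within-subjects correlation of 0.2". It closes with "To account for an expected 15-20% attrition, the total sample size is 100". No separate number before attrition is given.

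On the effect size, the section says that the pilot value for pain intensity (.82) "has been used as it had a lower effect size than the primary outcome (i.e., emotional dysregulation, effect size = .88"), and then powers on 0.7.

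Elsewhere, Section 2 makes emotion dysregulation the primary outcome and the post-assessment the primary endpoint. Section 8 measures that outcome with the DERS-18. Section 12 specifies a linear mixed model with time, group and their interaction. It will estimate between-group differences at 9 and 21 weeks, and changes from baseline within each group. Section 5 and the randomisation paragraph of Section 8 still give 48 as the number to be recruited, and both refer to Section 6.

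**The concern.** The number needed for analysis and the number to enrol differ whenever attrition is expected, and here 15-20% is expected. Giving 100 for both means that one of the two statements is wrong, and the reader cannot tell which. That decides whether the 80% applies to 100 people with data or to the 80 to 85 who are likely to be left.

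The missing contrast makes this worse. A correlation of 0.2 matters only if the calculation combines repeated measurements, and at 0.2 a change score is considerably noisier than a single measurement. The same 0.7 can therefore go with quite different power, depending on what is compared.

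Two smaller faults sit in the same paragraph. The pilot effect of .82 is said to have been used but 0.7 appears in the calculation. Also, the calculation is given only for pain intensity, so the detectable effect for DERS-18 has to be inferred.

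**Working it through.** **Inputs from Section 6.** Effect size d = 0.7; power 80%; alpha 0.05; within-subject correlation r = 0.2; attrition 15-20%; total 100 (50 per group). Sidedness is not stated, so two-sided is assumed. Attrition is taken as equal in the two groups.

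**Attrition arithmetic.**
- If 100 must be evaluable: 100 / 0.85 = 117.6, so 118 enrolled; 100 / 0.80 = 125 enrolled.
- If 100 are enrolled: 100 × 0.85 = 85 and 100 × 0.80 = 80 evaluable, i.e. 42.5 and 40 per group.

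**Reproducing the stated 100.** With variance multiplier v for the contrast (outcome SD = 1), the normal approximation is n per group = 2 × (1.960 + 0.842)² × v / d². The multipliers are:
- week-9 difference: v = 1;
- difference in change from baseline to week 9: v = 2(1 − r) = 1.6;
- mean of both post visits minus baseline: v = (1 + r)/2 + 1 − 2r = 0.6 + 1 − 0.4 = 1.2.

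These give 2 × 7.849 × v / 0.49 = 32.04, 51.26 and 38.44, rounded up to 33, 52 and 39 per group. The t-test versions are 34, 53 and 40. As a fourth reading, a 2-degree-of-freedom group-by-time F test over three visits, with group differences 0, 0.7 and 0.7, needs 48 per group.

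Power from the noncentral t (noncentral F in the last row), two-sided 0.05:

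| Contrast | n per group for 80% | Power at 50 per group | At 42.5 | At 40 |
|---|---|---|---|---|
| Week-9 difference | 34 | 93% | 89% | 87% |
| Difference in change to week 9 | 53 | 78% | 71% | 69% |
| Mean of both post visits minus baseline | 40 | 89% | 83% | 81% |
| Group-by-time, 2 df, three visits | 48 | 82% | 75% | 72% |

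The stated 100 can be approached in two ways:
- As an **evaluable** number with no attrition allowance: the change score (78% at 50 per group) and the 2-df interaction test (82%) both come within two points of 80%.
- As an **enrolled** number: the mean of both post visits minus baseline needs 40 per group by t-test, so 80 evaluable, and 80 / 0.80 = 100.

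The protocol names none of these as the basis of its calculation.

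**Detectable effect at 80% power.** For the week-9 difference it is 0.634 SD at 40 per group and 0.615 SD at 42.5. For the difference in change, multiply by √1.6 = 1.265: 0.634 × 1.265 = 0.80 and 0.615 × 1.265 = 0.78.

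**The case against.** A reader might infer that the design does not deliver 80% power. The documents do not support that. Section 2 makes the post-assessment the primary endpoint and Section 12 plans a between-group difference at 9 weeks. For that difference, power at 0.7 is 87-89% even after the stated attrition. The drop to about 69-75% arises only if the 0.7 belongs to a change-score or interaction contrast. The interaction in Section 12 makes that reading possible but does not establish it. There is also a reading, unnamed in the protocol, in which 100 is already the inflated figure. The fault would then be the claim that 100 are required, not the power.

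A reader might also infer that sizing on pain intensity leaves the primary hypothesis unpowered. That goes too far. Section 6 explains that pain had the smaller pilot effect (.82 against .88), so the choice is meant to be conservative. In standardised units the same number serves DERS-18 if its effect is at least 0.7 and, for contrasts that use it, the correlation is similar. Moving from .82 to 0.7 makes the sample larger, so it does no harm to power.

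All of this stands. It limits the point to the wording, the missing contrast and the missing statement for the primary outcome. It does not rescue the paragraph: 100 is still given two incompatible meanings.

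**Conclusion.** The contradiction is certain: 100 cannot be both the number required and the number after a 15-20% allowance. The size and direction of any power error are not certain, because the contrast is not named. With 80 to 85 completers, power at 0.7 runs from about 69-71% (difference in change to week 9) through 81-83% (mean of both post visits minus baseline) to 87-89% (week-9 difference).

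These figures assume a two-sided test, equal attrition, r = 0.2 where it enters, and 100 enrolled. They count completers only; the mixed model also uses baseline values from those who drop out, which would raise the change-score figure a little. They make no allowance for clustering within skills groups, for which the protocol gives no intraclass correlation. They also depend on 100 being the right total. At the 48 given in Sections 5 and 8 (24 per group), power before any attrition would be about 66% for the week-9 difference and 47% for the change score.

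This should be fixed, but it does not put the trial in doubt: it is a pilot, and the planned week-9 comparison keeps more than 80% power under the stated assumptions.

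**What to change.** Rewrite the Section 6 paragraph so that it:

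1. keeps 100 as the number enrolled and gives 80 to 85 as the expected number with week-9 data after 15-20% attrition, removing the claim that 100 are required for 80% power;
2. names the contrast from the Section 12 mixed model, and the sidedness of the test;
3. states power and detectable effect for DERS-18 at week 9 first, and pain intensity second. For the week-9 difference this would be 87-89% power at 0.7 SD and 80% power at about 0.61-0.63 SD. For the difference in change it would be 69-71% at 0.7 SD and 80% power at about 0.78-0.80 SD, provided that r = 0.2, which Section 6 states for the pain-intensity calculation, also holds for DERS-18;
4. replaces the statement that .82 was used with one saying that 0.7 is a conservative value below both pilot effects.

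Then reconcile the 48 participants in Section 5 and in the randomisation paragraph of Section 8 with the total in Section 6.

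The cost is one rewritten paragraph and two corrected cross-references, with no extra participants. If the intended contrast is the change score, the stated power will be lower than 80% and should be reported as such.
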